### Objectives

The three main aims of the DiAPAson study, a 36-month-long project, are as follows:

#### Objective 1

To evaluate the daily time use (e.g., use of time spent in different activities) of patients with SSD living in RFs compared to outpatients with SSD and to a large, normative sample of the general population; to assess the relationship between the severity of psychiatric symptoms (in particular negative symptoms) and the amount of time spent doing nothing and being sedentary.

#### Objective 2

To assess the quality of staff-patient relationships for patients living in RFs and its relationship with the staff’s well-being and burnout, and to evaluate the quality of RFs rated by service managers using the Quality Indicator for Rehabilitative Care – Supported Accomodation (QuIRC-SA).

#### Objective 3

To compare real-time ESM data about daily activities with retrospective, paper-and-pencil assessments to evaluate the consistency between these two data collection methodologies, and to assess levels of PA with a multi-sensor monitor (actigraphy) in three groups (RF patients and outpatients with SSD compared to healthy subjects).

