### Study 1 design

#### Participants

The sample will include 300 residential patients diagnosed with SSD (G1), matched by age and gender to 300 outpatients (G2). General population data will be extracted from the National Institute of Statistics (ISTAT) survey “*Uso del tempo quotidiano*”, a national survey that assesses how people spend their time, which was conducted in 2013 in Italy (ISTAT, https://www4.istat.it/it/prodotti/microdati#file_ricerca) in a representative sample of the Italian population including approximately 27,000 families (with a total of approximately 60,000 surveyed individuals) living in 508 municipalities (out of over 8000 Italian municipalities) of different sizes.

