### Data analyses

#### Study 1

Data on daily time use in the different groups will be compared using parametric and non-parametric methods depending on the distribution of the investigated variables. Correlation estimates (Pearson or Spearman) will be used to assess the associations between the severity of psychiatric symptoms and the amount of sedentary time.

Sample size was calculated based on Cella and colleagues’ study [12], which compared patients with SSD (*N* = 170) and a general population sample (*N* = 1124). Their results showed that the average time spent “doing nothing” (target) in the patient group was 5.17 h per day, while for the general population, it was 0.76 h with a standard deviation of 5 for both groups. With such data, the effect size for a linear model is 0.44. As a precaution, assuming a lower effect size equal to approximately 0.15, using ANCOVA (including age and gender in the model) with three groups, and choosing a power of 0.8, the estimated total sample size is equal to *N* = 435. Moreover, considering a total of approximately 25 different recruitment centres, the correction for the design effect (DE = 1 + (435/25–1)*0.02 = 1.3, with an intraclass correlation coefficient equal to 0.02) leads to a sample size of about *N* = 570, which was increased to *N* = 600 (300 for each group) to account for possible dropouts of about 10%. Finally, 300 matched subjects randomly sampled from the ISTAT general population sample will be added as third group, for a total of *N* = 900 subjects evaluated for daily time use.

#### Study 2

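### Study 1 limits the general-population comparator to one random draw of 300 from about 60,000 existing ISTAT respondents, an avoidable loss of precision and reproducibility but not a bias or a power failure

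*Protocol article*

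**What the plan says.** Objective 1 of the protocol article is to describe daily time use in residential patients "compared to outpatients with SSD and to a large, normative sample of the general population". Under Study 1 design, Participants, the source is named as the 2013 ISTAT time-use survey, a representative sample of about 27,000 families "with a total of approximately 60,000 surveyed individuals". The same section plans 300 residential patients matched by age and gender to 300 outpatients.

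The Study 1 paragraph of Data analyses then fixes the comparator: "300 matched subjects randomly sampled from the ISTAT general population sample will be added as third group", for a total of 900. The sample size rests on mean time spent doing nothing that "in the patient group was 5.17 h per day, while for the general population, it was 0.76 h". The SD is taken to be 5 h in patients and population alike. The planned model is given as "using ANCOVA (including age and gender in the model) with three groups, and choosing a power of 0.8". The article does not explain why the ISTAT group stops at 300.

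**The concern.** Equal group sizes are the natural choice when every subject costs the same to obtain. Here they do not: patients must be recruited, while the ISTAT records already exist. Matching on age and gender does not require one control per patient, since several matches, or all eligible respondents standardised to the clinical age and gender distribution, keep the same balance.

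Two things are at stake. The interval around each patient-versus-population difference is wider than the available data require. The reported population value also depends on which 300 people the draw selects, so two analysts following the same plan would report somewhat different reference figures. Patients versus the general population is the first hypothesis in the article, so this comparison deserves the best precision that the existing data allow.

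**Working it through.** **The plan's own figures.** From the cited means, f = (5.17 − 0.76)/(2 × 5) = 0.441, which agrees with the stated 0.44. For "assuming a lower effect size equal to approximately 0.15", three groups, two covariates, power 0.80 and alpha 0.05 (assumed, as the article does not state it), the noncentral F gives N = 432. Power at the stated 435 is 0.804, so the figure is reproduced. The design effect is 1 + (435/25 − 1) × 0.02 = 1.328.

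**Step 1: equal SDs, as the article assumes.** For one patient group of 300 against R ISTAT subjects, SE = 5 × √(1/300 + 1/R).

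| R | SE (h) | 95% half-width (h) | Reduction |
|---|---|---|---|
| 300 | 0.408 | 0.80 | – |
| 1,500 | 0.316 | 0.62 | 23% |
| 3,000 | 0.303 | 0.59 | 26% |
| 20,000 | 0.291 | 0.57 | 29% |
| limit | 0.289 | 0.57 | 29% |

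The number of respondents aged 20 to 55 is not given; 20,000 is an assumption. It hardly matters, because the gain is nearly flat beyond 3,000. With equal SDs, moving to 3,000 is worth as much as raising both groups from 300 to 2/(1/300 + 1/3,000) = 545.

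**Step 2: clustering and dropout among patients.** Six hundred patients over 25 centres is 24 per centre, or 21.6 after 10% dropout. The design effect is then 1 + 20.6 × 0.02 = 1.412, and 270/1.412 = 191 effective patients per group. The SE in SD units falls from √(1/191 + 1/300) = 0.0926 to √(1/191 + 1/3,000) = 0.0746, a reduction of 19%.

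**Step 3: equal SDs cannot hold for doing nothing.** A variable confined to 0–24 h with mean 0.76 h has SD at most √(0.76 × 23.24) = 4.2 h, reached only if everyone is at 0 or 24 h. Keep the patient SD at 5 h and let the population SD be s. The SE is √(25/n + s²/R), with n = 300, or n = 191 after step 2. The maximum gain compares R = 300 with R without limit.

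| s (h) | SE at R = 300, n = 300 (h) | Limit (h) | Maximum gain, n = 300 | Maximum gain, n = 191 |
|---|---|---|---|---|
| 4.2 (bound) | 0.377 | 0.289 | 23% | 17% |
| 3 | 0.337 | 0.289 | 14% | 10% |
| 2 | 0.311 | 0.289 | 7% | 5% |
| 1 | 0.294 | 0.289 | 2% | 1% |

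The SDs of 3, 2 and 1 h are assumptions; the article gives no other population SD.

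**Step 4: dependence on the draw.** The mean of 300 ISTAT subjects has SE s/√300: 0.24 h at the bound, and 0.17, 0.12 or 0.06 h at SDs of 3, 2 or 1 h. At 2 h, the 95% range is about ±0.23 h around a mean of 0.76 h.

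**Step 5: effect on the other contrast.** If a common residual variance is fitted to all three groups, a large ISTAT group dominates it. Take patient SD 5 h and ISTAT SD 2 h (illustrative). The correct SE for residential versus outpatient is 5 × √(2/300) = 0.408 h.

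- ISTAT 300: pooled variance (600 × 25 + 300 × 4)/900 = 18, SE 0.346 h, 15% too small.
- ISTAT 20,000: pooled variance (600 × 25 + 20,000 × 4)/20,600 = 4.61, SE 0.175 h, 57% too small.

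**The case against.** The strongest defence is that one-to-one matching is valid and sufficient. A random matched draw is unbiased and its sampling error is carried in the reported interval. At 300 against 300, power is near 100% for the cited 4.41 h difference, and 93–96% for a standardised difference of 0.3 (with and without the design effect of 1.328). It drops to 62–69% only at 0.2, a target that the article does not set. All of this stands, so a reader who infers that the first hypothesis is biased or underpowered goes further than the document supports.

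Equal group size also has a real merit under the planned three-group ANCOVA. As step 5 shows, it limits the damage from a common variance, so it would be wrong to say that it has no advantage. A larger ISTAT group helps only if the variance model is changed with it.

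A reader might also infer that less common activities such as study, voluntary work or sport will have too few non-zero values among 300 controls. The article gives no participation rate for any activity, so this cannot be shown.

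What the defence does not supply is a reason for stopping at 300. A valid interval can still be needlessly wide, and the stated objective promises a large comparator.

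**Conclusion.** The point holds as one of efficiency and reproducibility. The plan uses 300 records where many more exist, and so accepts wider patient-versus-population intervals and a reference value that varies with the draw.

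The size depends on the outcome. The SE reduction of 26% with 3,000 subjects (19% with 191 effective patients) rests on the article's equal SDs. That may suit other activities, but the document gives no SDs for them. It should not be read as the gain for doing nothing. There the ceiling is about 23%, and a gain of 2–14% follows if the population SD lies between 1 and 3 h. Those figures further assume a patient SD of 5 h and, before step 2 is applied, no clustering. The residential-versus-outpatient contrast gains nothing. The change is worth making because it is cheap, not because a conclusion is in danger.

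**What to change.** Replace the single draw of 300 by one of two options:

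- a higher matching ratio, for example 5 to 10 ISTAT respondents aged 20 to 55 for each matched residential–outpatient pair (1,500 to 3,000 in all), matched on age and gender;
- all eligible ISTAT respondents, standardised to the clinical age and gender distribution with the survey weights, and with allowance for several respondents from one family.

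With either option, fit group-specific residual variances, or estimate the residential-versus-outpatient contrast from the clinical groups alone, so that the ISTAT group does not set its standard error. If 300 is kept, give the reason.

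The change needs no patients and no new data collection. It does bring moderate extra analysis work, and the non-parametric tests that the article allows do not take survey weights simply. The matching option avoids much of that difficulty and, with equal SDs, already recovers most of the gain.

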Verona Service Satisfaction Scale (VSSS) (Ruggeri et al., 1993 [69])	Satisfaction with services	X			
Working Alliance Inventory Short Patient and Therapist versions (WAI-PT and WAI-TP) (Hatcher & Gillaspy, 2006 [70]; Lo Coco et al., 2011 [71])	Patients’ and staff relationships	X			X
Camberwell Assessment of Need Patient and Staff versions (CAN) (Phelan, 1995 [72]; Ruggeri et al., 1999 [73])	Health and social needs	X			X
Ward Atmosphere Scale (WAS) (Moos & Houts, 1968 [74]; Burti et al., 1990 [75])	Individual perception of the ward atmosphere	X			X
General Health Questionnaire (GHQ-12) (Goldberg, 1970 [76]; Fontanesi et al., 1985 [77])	General health evaluation				X
Maslach Burnout Inventory (MBI) (Maslach, 1981 [78]; Sirigatti et al., 1988 [79])	Level of Burnout				X
Quality Indicator for Rehabilitative Care (QuIRC-SA) (Killaspy, 2016 [80])	Quality of the rehabilitative service				X (RF’s manager)
Smartphone app	Use of daily time	X	X	X	
Smartphone app	Perceived energy	X	X	X	
Smartphone app	Mood	X	X	X	
Actigraphy	Physical activity	X	X	X	

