### Study 2 design

#### Participants

The sample will include 300 patients living in RFs (G1) and RF staff (approximately 1 staff member every 5 patients).

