To evaluate how the level of burnout of the staff affects the quality of the therapeutic relationships with the staff, correlation estimates (Pearson or Spearman) will be used. The influence of the burnout level (categorized as high/low) of staff (each staff member associated with a patient) on the quality of the therapeutic relationship with patients (WAI-pt) will be investigated by comparing groups (patients and staff in RFs) with generalized linear or linear models. To evaluate the associations between the quality of RFs rated by service managers and patient experiences of care, in accordance with Killaspy and colleagues [83], we will perform multilevel modelling analyses of associations between service user ratings (level 1 data) as dependent variables with unit QuIRC-SA domain ratings (level 2 data) as independent variables. The models will also include potential mediators (i.e., age, gender, and level of severity of psychiatric symptoms as assessed in Study 1).

#### Study 3

Appropriate tests will be used to compare the daily time use with routine methods and with ESM according to the distribution of the data. In particular, frequencies and corresponding chi-square tests, as well as Cohen’s kappa concordance index, will be used to compare ESM reports and retrospective assessments and to assess the degrees of consistency between the two sources of information.

The sub-sample chosen for Study 3 (*N* = 150, including 50 randomly chosen from Group 1, 50 randomly chosen from Group 2 and 50 healthy subjects) is in line with the sample size of Merikangas and colleagues [84]. Multilevel models (MLM [85]) will be used to simultaneously evaluate within- and between-subject associations, taking into account repeated measurements. In addition, cross-lagged analyses will be carried out to examine the directionality of the measured effects. Comparisons of PA quantity variables between groups will be evaluated using linear and generalized linear models.

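### Study 2 relates burnout, measured on about 60 staff, to patients' alliance ratings with methods that, as named, ignore shared staff and facilities, and one analysis splits burnout high/low without a cut-point

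*Protocol article*

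**What the plan says.** Study 2 design, Participants: "The sample will include 300 patients living in RFs (G1) and RF staff (approximately 1 staff member every 5 patients"). Table 2 marks the Maslach Burnout Inventory for staff only. It marks the Working Alliance Inventory for residential patients and staff, in a patient and a therapist version.

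Data analyses, Study 2, names two analyses of burnout against the therapeutic relationship:

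- For how staff burnout "affects the quality of the therapeutic relationships with the staff, correlation estimates (Pearson or Spearman) will be used". The article does not say which version of the alliance scale enters this step.
- "The influence of the burnout level (categorized as high/low) of staff (each staff member associated with a patient") on the patient-rated alliance score "will be investigated by comparing groups (patients and staff in RFs) with generalized linear or linear models". No cut-point for high and low is given.

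No random effect, generalized estimating equation or robust variance is mentioned for either. For the other Study 2 question, facility quality against patients' experience of care, the same section says "we will perform multilevel modelling analyses of associations between service user ratings (level 1 data) as dependent variables", with the facility ratings at level 2.

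**The concern.** The link between burnout and the staff-patient relationship is part of Objective 2 and is a stated hypothesis. Burnout takes one value per staff member. If that value is attached to each of about five patients, the comparison is between staff, and patients who rate the same staff member are likely to give similar alliance scores. Ordinary correlation tests and single-level linear models take the observations as independent, so their standard errors would be too small and false positives too frequent. If the therapist version of the scale is used, one person supplies both the burnout score and about five of the alliance ratings, which makes the dependence more direct. Facility clustering comes on top.

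Splitting a score into high and low also discards information, and an unstated cut-point can be chosen after the data are seen.

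**Working it through.** **The article's own figures.** Study 2 has no sample-size calculation; its 300 patients come from Study 1. That calculation can be reproduced. An ANCOVA with effect size 0.15, three groups, two covariates and power 0.80 needs N = 432 (435 stated; two-sided alpha of 0.05 assumed, since none is given). The design effect is 1 + (435/25 − 1) × 0.02 = 1.328 (1.3 stated), and 435 × 1.3 = 566 (about 570 stated). So the article corrects for centre clustering in Study 1, with an ICC of 0.02.

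**Inputs for the burnout question.**
- 300 patients and about one staff member per five: 300/5 = 60 staff (Study 2 design, Participants).
- Burnout is constant within a staff member (Table 2).
- Staff-level ICC of the alliance score: not given. Assumed range 0.02 to 0.30. The low end is the Study 1 centre value, which was set for time use by centre and is not evidence about alliance ratings of a shared staff member.
- Two-sided 5% test: assumed.

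**Formulas,** for five patients per staff member and an exposure constant within staff:
- DE = 1 + (5 − 1) × ICC
- effective n = 300/DE
- the correct standard error is √DE times the naive one
- actual type I error = 2 × (1 − Φ(1.96/√DE))

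| ICC | DE | Effective n | √DE | Actual type I error |
|---|---|---|---|---|
| 0.02 | 1.08 | 278 | 1.04 | 5.9% |
| 0.05 | 1.20 | 250 | 1.10 | 7.4% |
| 0.10 | 1.40 | 214 | 1.18 | 9.8% |
| 0.20 | 1.80 | 167 | 1.34 | 14.4% |
| 0.30 | 2.20 | 136 | 1.48 | 18.6% |

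Facility clustering is not in this table and would add to it.

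**Simulation.** 60 staff with five patients each, no true association, 4,000 runs per ICC:

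| ICC | Pearson on 300 pairs | High/low (median) t-test on 300 patients | Correlation on 60 staff means |
|---|---|---|---|
| 0 | 4.9% | 4.8% | 4.9% |
| 0.10 | 9.4% | 9.4% | 4.7% |
| 0.20 | 13.2% | 14.7% | 4.5% |
| 0.30 | 19.2% | 20.3% | 5.0% |

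The simulation agrees with the formula. Analysing staff means removes the excess, so the excess comes from ignoring the shared staff member.

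**High/low split.** For a normally distributed score, the share of information kept is φ(c)²/(p(1 − p)), where c is the cut-point and p the proportion on one side. This gives 64% at a median split, 58% at 30/70, 54% at 25/75 and 49% at 20/80.

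**The one-to-one reading.** If each staff member is paired with a single patient, there are about 60 pairs, the staff-level design effect is 1, and 300 − 60 = 240 patients are unused. The smallest correlation detectable with 80% power, tanh((1.96 + 0.84)/√(n − 3)), is then 0.35, against 0.16 with 300 independent pairs.

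**The case against.** The article is a condensed account, and naming linear or generalized linear models names a family. Random effects or robust variances are often left to the full plan. The investigators know about clustering, as Study 1 and the QuIRC-SA analysis show. Independence is therefore inferred from the methods named and nowhere stated. This part stands, and a reader should not conclude that the article declares 300 independent observations. But a section that sets out levels 1 and 2 for one Study 2 question and single-level methods for the other has fixed a method, and fixed it badly.

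The pairing phrase could mean one patient per staff member, which removes the staff-level problem. That fits poorly with 300 patients at one staff member per five and would leave most patients unused. The ambiguity is real and needs resolving in either direction.

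Three stronger readings are tempting, and the documents do not support them:

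- *That p-values are certainly and badly too small.* The size depends on an ICC the article does not give. At 0.02 the true error is 5.9%.
- *That the effective sample size is 60.* With five patients per staff member this needs DE = 5, that is ICC = 1. Over the range above it is 136 to 278.
- *That both analyses discard information by dichotomising.* High/low is attached to the second only; the correlation presumably uses the score itself.

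**Conclusion.** The point holds in conditional form. Burnout varies over about 60 staff, and the two analyses named for it make no allowance for shared staff or facilities. If about five patients share each staff member, a nominal 5% test has a true error of about 6% at ICC 0.02, 7% at 0.05, 10% at 0.10, 14% at 0.20 and 19% at 0.30. Understatement of the standard errors is minor at the low end and material from about 0.10. These figures assume equal groups of five, a two-sided 5% test and no additional facility effect.

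The high/low split is a separate, lesser fault of the second analysis. It costs at least about 36% of the information (100% − 64%) if the score is normal, and the missing cut-point leaves room for choice after the data are seen.

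**What to change.** In Data analyses, Study 2:

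1. State how staff and patients are linked: one-to-one pairs or about five patients per staff member.
2. Make the main analysis a regression of the patient-rated alliance score, and separately the staff-rated one, on the continuous burnout score, with a method that respects clustering by staff member and facility. Any of these would do: a mixed model with a staff random intercept, plus a facility term if estimable; cluster-robust inference with a small-sample correction; or an analysis of staff means. Fully nested random intercepts should not be the only option: 60 staff over about 25 centres is about 2.4 per centre, and the two variances may be hard to separate.
3. Adjust for patient age, gender and symptom severity, which are already collected and already planned for the QuIRC-SA models.
4. Keep high/low for description, with the cut-point stated in advance.
5. Say that the exposure varies over only about 60 staff, without calling 60 the effective sample size.

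The cost is analysis wording only. No new data are needed, provided the identity of each patient's rated staff member is recorded, as the plan to associate staff with patients implies. Confidence intervals will be somewhat wider, by the √DE factors above.

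### The Study 2 burnout analysis names patients and staff as the groups to compare, which does not test burnout and cannot be formed on the patient-rated outcome; the model should compare WAI-PT by staff burnout and allow for shared staff

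*Protocol article*

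**What the plan says.** Under Data analyses, Study 2, one sentence gives the whole burnout model:

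- **Factor:** "The influence of the burnout level (categorized as high/low) of staff", with the link to patients described as "each staff member associated with a patient".
- **Outcome:** the effect is to be judged "on the quality of the therapeutic relationship with patients (WAI-pt"), the patient version of the Working Alliance Inventory. No other outcome is named.
- **Comparison and method:** it "will be investigated by comparing groups (patients and staff in RFs) with generalized linear or linear models".

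The sentence before it plans a Pearson or Spearman correlation between staff burnout and relationship quality. The sentence after it specifies multilevel modelling, but only for the QuIRC-SA ratings.

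Three other places bear on this. Table 2 lists "Working Alliance Inventory Short Patient and Therapist versions (WAI-PT and WAI-TP"). The Recruitment and data collection section puts WAI-PT among the tools patients complete themselves and WAI-TP among those clinicians complete. The Study 2 Participants paragraph says "The sample will include 300 patients living in RFs (G1") plus staff at "approximately 1 staff member every 5 patients".

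**The concern.** The question asked is whether patients report a poorer alliance when their staff member is burned out. Answering it needs two sets of patients, defined by the burnout of the staff member linked to them. The sentence names patients and staff instead. A difference between those two shows whether the two sides rate the relationship differently, not whether burnout matters. Staff have no WAI-pt score, so the comparison is also impossible on the stated outcome.

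Once the groups are put right, a second problem appears. Burnout is measured on the staff member and shared by all patients linked to that person. An ordinary linear or generalized linear model on patient rows counts 300 independent burnout exposures where there are about 60.

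The relation between staff burnout and the staff-patient relationship is part of Objective 2 and a stated hypothesis. A false positive here would attribute poorer alliance to staff burnout on evidence thinner than its p-value suggests.

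**Working it through.** The article gives no sample size, power or effect size for Study 2, so there is no figure of its own to reproduce.

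**Step 1: can the named contrast answer the question?**

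| Element | What the article gives | What the burnout question needs |
|---|---|---|
| Factor | staff burnout, high or low | the same |
| Outcome | WAI-pt | the same |
| Groups | patients; staff | patients with a high-burnout staff member; patients with a low-burnout staff member |
| Who has a score on the outcome | patients only | patients only |

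Only the third row is out of line. Suppose the patient-versus-staff contrast were forced by bringing in the staff version. In a simulation of 60 staff with 5 patients each (4,000 runs per setting), a true burnout effect of -0.5 SD acted equally on both ratings. The mean patient-staff difference stayed within 0.005 SD of zero, and the test rejected in about 2% to 4% of runs. The high-versus-low burnout comparison on the same data rejected in about 95% to 99%. So the named contrast carries no information on a burnout effect common to both raters.

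**Step 2: the dependence on the sensible reading.**

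Inputs from the article: 300 patients and about 5 patients per staff member, so 300 / 5 = 60 staff. Assumed, because the article does not give them for Study 2: two-sided alpha 0.05, and a staff-level ICC of WAI-pt between 0.02 and 0.30. The low end equals the centre-level ICC used in the Study 1 sample size. Equal clusters of 5 are also assumed.

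Formulas:

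- Design effect: DE = 1 + (5 - 1) × ICC
- Effective number of patients: 300 / DE
- True alpha of the unclustered test: 2 × [1 - Φ(1.96 / √DE)]
- Difference detectable with 80% power, equal groups, in SD: 2 × 2.80 / √(300 / DE)

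| ICC (assumed) | DE | Effective N | True alpha (formula) | Rejection rate, no true effect (simulation) | Detectable difference, SD |
|---|---|---|---|---|---|
| 0.02 | 1.08 | 278 | 0.059 | 0.061 | 0.34 |
| 0.10 | 1.40 | 214 | 0.098 | 0.107 | 0.38 |
| 0.20 | 1.80 | 167 | 0.144 | 0.142 | 0.43 |
| 0.30 | 2.20 | 136 | 0.186 | 0.195 | 0.48 |

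If all 300 patients were treated as independent, the detectable difference would appear to be 2 × 2.80 / √300 = 0.32 SD.

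Formula and simulation agree to about 0.01. Clustering of staff within facilities is not included in these figures.

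**The case against.** The best defence is that the parenthesis is only loose wording. The same sentence names the factor, the link and the outcome, and together they point to patients compared by their staff member's burnout. Patients and staff may then simply be the people who supply the data: staff give the burnout score and patients give WAI-pt. No hypothesis in the article concerns disagreement between raters. This is probably what was meant. It does not rescue the text, because the parenthesis is attached to the groups being compared and names the wrong ones.

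A second defence is that the preceding sentence plans a correlation between burnout and relationship quality, so the association is examined in any case. That stands: the faulty sentence is one of two burnout analyses. The correlation would face the same sharing of staff scores if run on patient rows.

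A third defence is that this is a condensed article, and random-effects structure is commonly left to the analysis plan. That tempers the clustering part, since the full plan may already contain those terms. It does not excuse the group label, which is stated and not merely missing. The article also says multilevel where it means it, for QuIRC-SA in the next sentence and for Study 3, while here it names only linear or generalized linear models.

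A reader might go further and infer that the plan compares WAI-PT with WAI-TP as two independent samples, ignoring that each pair describes one relationship, or pools both so that each dyad counts twice. The document does not support this. WAI-TP is named nowhere in the Data analyses section, the only outcome is WAI-pt, and nothing says that two sets of ratings are treated as independent. With WAI-pt alone there is one score per patient, and no pair to mishandle.

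**Conclusion.** The concern holds in limited form. The sentence is internally contradictory: the groups it names do not match its factor and cannot both be scored on its outcome. That conclusion comes from the text alone and needs no assumption.

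On the reading that makes sense of the sentence, an ordinary model on patient rows would understate the standard error of the burnout effect. The size depends on an ICC the article does not give. The true alpha would be about 0.06 if the ICC is as small as 0.02 and about 0.19 if it is 0.30, given five patients per staff member and no extra facility effect. If the full analysis plan already models staff and facility, this second part falls away and only the wording needs repair.

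No error rate or loss of power from mishandled pairs of alliance ratings should be charged to the plan, because it states no such analysis. The point should be corrected before analysis; it does not affect data collection.

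**What to change.** 1. Replace the named groups with the burnout groups: WAI-PT compared between patients whose linked staff member has high burnout and those whose linked staff member has low burnout, one row per patient.
2. Fit this as a mixed model with random intercepts for staff member and facility, or use cluster-robust standard errors.
3. Reconcile the link wording with the Study 2 Participants paragraph by saying that one staff member is linked to several patients, about five on average.
4. Only if WAI-TP is also to be analysed, put both ratings in one model with rater as a within-dyad factor, a rater-by-burnout term and a dyad random intercept, and report the burnout effect separately for each rater.

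The cost is a wording change and a slightly larger model. Both WAI versions and the burnout inventory are already collected. Burnout p-values will be somewhat less favourable than from an unclustered model.
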